### **8.3. Protocol Deviations**

Protocol deviations will be collected throughout the duration of the study. Protocol deviations will be assigned a sponsor-defined category type. In addition, each deviation will be defined as significant or minor. A tabular summary of all significant deviations will be generated. In addition, a by-subject listing of all protocol deviations (significant and minor) will be produced.

## **9. Methods of Efficacy Analysis**

Since the study's primary aim is to demonstrate non-inferiority in mean daily weight gain (g/day) between the formula groups, the Per Protocol Population will represent the primary analysis population to evaluate the formula groups in terms of "efficacy". All clinical outcomes (primary and secondary) will be subject to analyses using both the PP and ITT Populations. Analyses using the PP and ITT Populations will be based on the formula the infant is randomized to.

The primary efficacy variable is the mean daily weight gain (g/day) over a 16-week study period. Secondary variables for efficacy to be considered include:

- Anthropometric measures
- Formula intake volume

Efficacy endpoints will be summarized by study visits at study sites. The protocol schedule of assessment lists target visit days that occur every 15 or 30 days and associated tests to be conducted on these visits and also specify associated visit windows (+/- 3 days) for these visits. However, it is not uncommon for subjects to have visits outside the protocol specified visit windows due to various reasons. Because of this, analysis visits and windows are specified below to include as much data as possible in the analyses. While presenting summaries of data by visit, analysis visits will be used according to the windows specified below. Using the analysis visits and windows allow for more comparable comparisons of test results which are closest to the protocol specified target visits and time on study formula while correcting for possible issues that occurred during the study.

| Analysis Visit | Target Day | Window    |
|----------------|------------|-----------|
| 1              | 0          | N/A       |
| 2              | 15         | 8 – 22    |
| 3              | 30         | 23 – 44   |
| 5              | 60         | 45 – 74   |
| 7              | 90         | 75 – 104  |
| 9              | 120        | 105 – 134 |

Analysis relative day (ADY) will be derived and used to determine the appropriate analysis visit. The subject's randomization date (ADY = -1) will be used to calculate the treatment start day (ADY = 1) and the analysis relative day for each study visit. ADY will be used to compare to the analysis visit target day to identify the analysis visit. If more than one visit falls within a window, then the visit closest to the target day will be used in the analysis (ANL02FL = Y). If more than one visit falls within a window and they are the same distance to the target day, then the latest visit will be used in the analysis. Unscheduled assessments will be assigned to the associated analysis visit based on date and time of assessment.

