**Visit 9 (Day 120  $\pm$ 3 days)**

- Medical history
- Anthropometry
- Stool Characteristics and Tolerance Questionnaire
- Infant Characteristics Questionnaire
- 3-day Formula/Diet Record
- Blood Collection
- Stool collection
- Medication
- Adverse events
- Collection of all unused/partially used study formula

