### **6.8. Adjustments for Covariates**

Adjustments for sex, age at enrollment, baseline values, formula, visit, pooled site, formula by pooled site interaction, and formula by visit interaction will be made for statistical analyses. If the model does not converge when using all these covariates, then the formula by pooled site interaction term will be dropped from the model.

Some of the sites have very few subjects. All sites in the same state will be grouped together and then states will be grouped together geographically into a new pooled site variable.

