## 9.1. Primary Efficacy Analysis

The primary efficacy endpoint, mean daily weight gain (g/day) over the 16-week study period and at each study visit, will be calculated as (average weight in grams at each study visit – average weight in grams at baseline visit)/number of days since baseline visit. The weight is measured a minimum of two times at each study visit (a third weight is measured if the first two do not meet the threshold specified in the protocol). If two measurements are taken, then the average of the two will be used in the preceding formula. If there are more than two measurements, then the two measurements that are the closest will be averaged and used in the preceding formula. If three measurements are equidistant, then the lower two measurements will be averaged and used in the preceding formula. If there are less than 2 measurements recorded, then the average weight measurement will be set to missing. This average weight measurement will be used in the calculation for mean daily weight gain above. Descriptive statistics of the mean daily weight gain will be presented by visit and formula group. Mean daily weight gain at visit 9 (Day 120) will be compared between BBN-102 w/o OPN and the Brand Formula with a mixed-effect model for repeated measures (MMRM). The test for non-inferiority of the primary efficacy endpoint will have the following hypotheses:

H0: The difference (BBN-102 w/o OPN – Brand Formula) in mean daily weight gain between the formula groups is less than or equal to -3 g/day at visit 9 (Day 120).

H1: The difference (BBN-102 w/o OPN – Brand Formula) in mean daily weight gain between the formula groups is greater than -3 g/day at visit 9 (Day 120).

Formula groups will be compared using a MMRM with sex, age at enrollment, baseline value, formula, visit, pooled site, formula by pooled site interaction, and formula by visit interaction as factors. The covariance matrix will be chosen based on the Akaike Information Criterion (AIC) to choose the covariance matrix that best fits the model. Non-inferiority will be determined if the lower limit of the two-sided 95% CI for the difference (BBN-102 w/o OPN – Brand Formula) in least square means is greater than -3, assuming a non-inferiority margin of 3 g/day.

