### **9.2.3. Growth measurements**

The growth measurements for weight, length, and head circumference will be collected at visits 1, 2, 3, 5, 7, and 9. The weight, length, and head circumference are each to be measured a minimum of two times at each study visit (a third measurement is taken if the first two do not meet the threshold specified in the protocol). If two measurements are taken, then the average of the two will be used. If there are more than two measurements, then the two measurements that are the closest will be. If three measurements are equidistant, then the lower two measurements will be averaged. If there are less than 2 measurements recorded, then the average weight measurement will be set to missing.

Descriptive statistics of the average growth measurements (weight, length, and head circumference) will be presented by visit and formula group. A MMRM analysis will be used to compare measures between formula groups at visit 9 (Day 120). The test for statistical difference of the growth measurements between formula groups will have the following hypotheses:

H0: There is no difference in the mean growth measurement between the formula groups at visit 9 (Day 120).

H1: There is a difference in the mean growth measurement between the formula groups at visit 9 (Day 120).

Formula groups will be compared using a MMRM with sex, age at enrollment, baseline value, formula, pooled site, visit, formula by pooled site interaction, and formula by visit interaction as factors. The covariance matrix will be chosen based on the AIC criteria to

choose the covariance matrix that best fits the model. 95% confidence intervals and p-values will be reported on the difference of least square means for comparison of formula groups.

Growth measures will be plotted for each subject over time.

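### Counting Day 105–134 as Visit 9 leaves raw size uncorrected for timing, and a shift in visit timing between the two phases would bias the primary contrast by a modest amount

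*Supplement*

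**What the plan says.** Protocol version 5.2 (section 9.2) schedules Visit 9 at Day 120 ±3, and the flowchart in SAP V4 (4.1) repeats this. For analysis, SAP V4 section 9 widens the Visit 9 efficacy window to Day 105–134. The stated purpose is that "analysis visits and windows are specified below to include as much data as possible in the analyses". If several visits fall in the window, "the visit closest to the target day will be used in the analysis (ANL02FL = Y".

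The primary analysis (9.1) is labelled by the target day: "Mean daily weight gain at visit 9 (Day 120) will be compared between BBN-102 w/o OPN and the Brand Formula". The endpoint is weight change since baseline over actual elapsed time: "average weight in grams at baseline visit)/number of days since baseline visit". Length and head circumference velocities (9.2.1) are built the same way. Raw weight, length and head circumference at Visit 9 (9.2.3) are analysed as measured and tested for a difference.

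On model terms, 9.1 says "Formula groups will be compared using a MMRM with sex, age at enrollment, baseline value, formula, visit, pooled site", followed by the two formula interactions; 6.8, 9.2.1 and 9.2.3 list the same set. Visit is a category. Age enters only as age at enrollment. There is no term for study day or age at measurement, and none for phase. The two sensitivity analyses of the primary endpoint (9.1.1) exclude COVID-19-affected infants and apply multiple imputation; neither concerns visit timing.

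**The concern.** Two infants measured up to 29 days apart (134 − 105) can both count as Day 120. Daily gain falls over the first months, so cumulative g/d is lower the later it is measured, while raw size is larger. A difference between arms in mean Visit 9 day would therefore move velocity and raw size in opposite directions.

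Randomization does not fully protect against such a difference here. Section 5 of the SAP plans 139 Brand infants, 129 of them from phase one, while all 86 BBN-102 infants are in phase two. If visit timing changed between phases, the change would fall mainly on the formula contrast. The SAP itself says out-of-window visits are not uncommon (section 9), expects COVID-19 disruption (6.4.1), and accepts that the enrollment periods need checking (9.1.2). At stake are the size of the primary difference in a non-inferiority decision and the reading of the raw-size comparisons.

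**Working it through.** **Inputs from the documents.** Visit 9 window Day 105–134 (SAP section 9); scheduled Day 120 ±3 (protocol 9.2); margin 3 g/d, SD 6.0 g/d, 104 Brand and 64 BBN-102 evaluable, one-sided alpha 0.025, power about 90% (SAP section 5). The documents give no growth curve, no distribution of visit days and no figure for the effect of timing.

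**The plan's own figure.** SE = 6.0 × √(1/104 + 1/64) = 0.953 g/d. Power at no true difference = Φ(3/0.953 − 1.96) = Φ(1.19) = 88.2%, close to the stated 90%. This SE is used below.

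**How a phase shift reaches the arms.** If phase-two visits run d days later than phase-one visits in both formulas, the Brand mean shifts by d × 10/139 and the BBN-102 mean by d. The arm difference is d × 129/139 = 0.93d, so a 5-day shift between phases becomes 4.6 days between arms.

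**Effect on velocity (assumed curve 1).** Let daily gain fall linearly, r(t) = a − bt. Cumulative velocity is V(t) = a − bt/2, which falls by b/2 per day of delay.

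| Gain at Day 0 → Day 120 (assumed, g/d) | b/2 (g/d per day) | 3-day arm difference | 5-day arm difference | One infant, Day 105 vs 134 | One infant, Day 117 vs 123 |
|---|---|---|---|---|---|
| 40 → 16 | 0.100 | 0.30 | 0.50 | 2.90 | 0.60 |
| 36 → 20 | 0.067 | 0.20 | 0.33 | 1.93 | 0.40 |
| 34 → 24 | 0.042 | 0.13 | 0.21 | 1.21 | 0.25 |

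**Effect on velocity (assumed curve 2).** Let A be mean gain to Day 120 and v the gain rate within the window: V(T) = [120A + v(T − 120)]/T, with slope about (v − A)/120. For A = 28 and v = 17–20, the fall is 0.067–0.092 g/d per day: 0.20–0.27 for 3 days, 0.33–0.46 for 5 days. Over A = 26–32 and v = 14–23 the range is 0.08–0.45 for 3 days and 0.12–0.75 for 5 days. If growth were linear (v = A), the effect would be zero.

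**Effect on the decision.** If the bias favours BBN-102 (its visits earlier), one-sided type I error is 1 − Φ(1.96 − bias/0.953): 5.0% for 0.3 g/d and 7.6% for 0.5 g/d, against 2.5%. If it goes the other way, power falls from 88% to 81% and 75%. Under curve 1, a bias of 0.3 g/d needs an arm difference of 3, 4.5 or 7.2 days (0.3 divided by 0.100, 0.067 or 0.042).

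**Effect on variance.** With visits spread evenly over Day 105–134 in both arms, SD rises from 6.0 to at most 6.14 and power falls from 88.2% to no lower than 86.7%.

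**Effect on raw weight.** Curve 1 gives 467–697 g between Day 105 and Day 134, or 16–24 g per day after dividing by 29; curve 2 goes down to 14 g per day. A 3–5 day arm difference is then 3 × 14 = 42 g to 5 × 24 = 120 g, with nothing in the model to remove it.

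**The case against.** The strongest reply is that the primary endpoint already accounts for elapsed time through its denominator, that Visit 9 is still scheduled at ±3 days, and that the wide window only catches stragglers, with the visit nearest the target chosen. That stands: only the residual from slowing growth is left in the velocities, and with like timing in both arms the bias is about zero.

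A reader might infer from the one-infant column (1.2–2.9 g/d) that the window can use up 40–97% of the margin. The documents do not support that. The margin applies to a difference between arm means, and such a shift would need one whole arm at Day 105 and the other at Day 134. In the central case of curve 2, a 3 g/d bias would need a mean difference of 33–45 days, more than the window holds. A reader might also infer a material loss of power from added variance, or set raw size against 3 g/d. The first is negligible, and the margin does not apply to raw size.

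Other safeguards help in part. The COVID-19 exclusion removes infants recorded as affected, but not timing shifts from other causes. The per-protocol definition (section 7) limits withdrawal weights entering as Visit 9, so that route (protocol section 21) concerns mainly ITT. The z-scores for weight, length and head circumference give each raw measure an age-referenced counterpart. Section 9.1.2 compares Brand growth between phases, but not visit day, and with about 10 phase-two Brand infants the half-width of a 95% interval is about 1.96 × 6.0/√10 = 3.7 g/d, too wide to reveal a shift of 0.1–0.5.

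Finally, a single day slope across all visits would be misspecified, since daily gain itself changes, and visit day is observed after randomization. Both points shape the fix.

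**Conclusion.** The gap is real but narrow. Raw weight, length and head circumference labelled Day 120 have no correction for the day they were taken. The velocities have one, through the denominator, that is exact only for linear growth. A 3–5 day difference in mean Visit 9 day between arms would shift the primary contrast by about 0.1–0.5 g/d (3–17% of the margin; up to 0.75 at the extreme of the assumed range) and raw weight by about 14–24 g per day of difference.

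These sizes rest on assumed growth curves. Whether timing differs between arms is unknown, and nothing in the documents shows that it does. The point merits action because the contrast is largely non-concurrent, because 0.3 g/d would roughly double the one-sided 2.5% error, and because the plan contains nothing that would reveal or correct a timing difference.

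**What to change.** - Keep the Day 105–134 window for data capture.
- Tabulate actual Visit 9 day by formula and phase. This alone would show whether there is a problem.
- Pre-specify one sensitivity analysis of the primary contrast restricted to Visit 9 weights taken on Day 117–123.
- In the raw-size models (9.2.3), add deviation of actual day from the target day as a covariate, with a slope allowed to differ by visit. Use the same term as a supportive analysis only for 9.1 and 9.2.1, where the denominator already does most of the work.

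The cost is SAP wording, one table and a few extra model terms, all from dates already collected. The restricted analysis will have fewer infants and a wider interval, so it should be read for consistency of the estimate and not as a second non-inferiority test.

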## 9.1. Primary Efficacy Analysis

The primary efficacy endpoint, mean daily weight gain (g/day) over the 16-week study period and at each study visit, will be calculated as (average weight in grams at each study visit – average weight in grams at baseline visit)/number of days since baseline visit. The weight is measured a minimum of two times at each study visit (a third weight is measured if the first two do not meet the threshold specified in the protocol). If two measurements are taken, then the average of the two will be used in the preceding formula. If there are more than two measurements, then the two measurements that are the closest will be averaged and used in the preceding formula. If three measurements are equidistant, then the lower two measurements will be averaged and used in the preceding formula. If there are less than 2 measurements recorded, then the average weight measurement will be set to missing. This average weight measurement will be used in the calculation for mean daily weight gain above. Descriptive statistics of the mean daily weight gain will be presented by visit and formula group. Mean daily weight gain at visit 9 (Day 120) will be compared between BBN-102 w/o OPN and the Brand Formula with a mixed-effect model for repeated measures (MMRM). The test for non-inferiority of the primary efficacy endpoint will have the following hypotheses:

H0: The difference (BBN-102 w/o OPN – Brand Formula) in mean daily weight gain between the formula groups is less than or equal to -3 g/day at visit 9 (Day 120).

H1: The difference (BBN-102 w/o OPN – Brand Formula) in mean daily weight gain between the formula groups is greater than -3 g/day at visit 9 (Day 120).

Formula groups will be compared using a MMRM with sex, age at enrollment, baseline value, formula, visit, pooled site, formula by pooled site interaction, and formula by visit interaction as factors. The covariance matrix will be chosen based on the Akaike Information Criterion (AIC) to choose the covariance matrix that best fits the model. Non-inferiority will be determined if the lower limit of the two-sided 95% CI for the difference (BBN-102 w/o OPN – Brand Formula) in least square means is greater than -3, assuming a non-inferiority margin of 3 g/day.

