## 5. Determination of Sample Size

Approximately 352 healthy term infants will be enrolled in both phases of the study to complete a minimum of 264 evaluable infants.

Formula fed infants will be randomly allocated to one of the three study formulas (BBN-001 w/ OPN, BBN-102 w/o OPN, Brand Formula) via IWRS (Interactive Web-Based Randomization System). Randomization will be blocked by formula group and stratified by infant sex to allow for balance in the number of males and females in each formula group.

Sample size estimation is based on a test for non-inferiority of the primary efficacy endpoint, mean daily weight gain (g/day), over a 16-week study period. Mean daily weight gain will be compared between formula groups by the calculation of the 95% confidence interval on the difference between the two means. A non-inferiority margin of -3 g/day is set for the difference in mean daily weight gain for the formula-fed groups. Non-inferiority is established, at the one-sided  $\alpha=0.025$  significance level, if the lower limit of the two-sided 95% confidence interval on the difference between the two least square means (BBN – Brand) is above -3 g/day.

For phase one of the study, sample size estimation is based on a test for non-inferiority between BBN-001 w/OPN Formula and Brand Formula. Assuming a standard deviation in mean daily weight gain of 5.6 g/day (Nelson et al., 1989) and 80% power, 90 subjects per group (180 total subjects) will be sufficient to demonstrate non-inferiority (one sided  $\alpha=0.025$ ). Assuming a 25% attrition rate, a total of 256 subjects will be enrolled in the BBN-001 w/ OPN Formula and Brand Formula groups.

For phase two of the study, sample size estimation is based on a test for non-inferiority between BBN-102 w/o OPN Formula and Brand Formula. A blinded interim analysis of 81 subjects who completed 16 weeks of the study was performed in phase one of the study to estimate the standard deviation of mean daily weight gain (g/day). Based on this analysis, it is assumed that the standard deviation in mean daily weight gain is 6.0 g/day. Assuming this standard deviation and approximately 90% power, approximately 168 subjects (64 in the BBN-102 w/o OPN Formula group and 104 in the Brand Formula group) will be sufficient to demonstrate non-inferiority (one-sided  $\alpha=0.025$ ). Assuming a 25% attrition rate, a total of approximately 96 subjects will be enrolled in phase two.

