The plan is to use the 129 subjects randomized to Brand Formula in the first phase of the study. Assuming a 25% attrition rate, we estimate 96 subjects will meet the Per Protocol (PP) population criteria. This data will remain blinded through the enrollment of phase

two of the study. In phase two of the study, infants will be randomized to Brand Formula or BBN-102 w/o OPN in a 1:8 ratio. Assuming a 25% attrition rate and to obtain at least 90% power, approximately 10 subjects randomized to Brand Formula and 86 subjects randomized to BBN-102 w/o OPN Formula will be enrolled in phase two of the study. With the addition of the 129 subjects from phase one of the study, there will be approximately a total of 139 subjects enrolled in the Brand Formula group and 86 subjects in the BBN-102 w/o OPN Formula group. Infants will be stratified by sex to achieve balance of males and females within each formula group.

At the conclusion of the study, a post-hoc power analysis on weight gain will be conducted.

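### The primary MMRM carries a formula-by-pooled-site interaction with no stated region weights or minimum cell size; uneven regions would cost power, and the non-convergence fallback does not cover a converged but non-estimable contrast

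*Supplement*

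**What the plan says.** SAP V4 section 9.1 compares BBN-102 w/o OPN with Brand Formula at Day 120 by an MMRM. Its terms are sex, age at enrollment, baseline value, formula, visit and pooled site, plus "formula by pooled site interaction, and formula by visit interaction as factors". Non-inferiority is declared if the lower 95% limit for the difference in least square means lies above -3 g/day.

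Section 6.8 explains the pooling: "Some of the sites have very few subjects". The rule is: "All sites in the same state will be grouped together and then states will be grouped together geographically into a new pooled site variable". It gives no number of regions, no map and no minimum number of infants per formula per region. The only fallback is: "If the model does not converge when using all these covariates, then the formula by pooled site interaction term will be dropped".

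Three features from section 5 matter here:

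- "Randomization will be blocked by formula group and stratified by infant sex"; site and region are not strata.
- "The plan is to use the 129 subjects randomized to Brand Formula in the first phase of the study".
- Phase two allocates infants to Brand Formula "or BBN-102 w/o OPN in a 1:8 ratio", giving about 10 Brand and 86 BBN-102 infants.

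Section 6 names SAS 9.4 or higher. No section names a weighting option for the least square means.

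**The concern.** With a formula-by-region term in the model, there is no single formula effect. The least-squares-mean difference is an average of region-specific differences, and someone must choose the weights. The SAP does not. The customary software default weights every region equally, so a region with a handful of infants counts as much as the largest one. The variance of the contrast is then driven by the smallest cells. The sample size in section 5 is a comparison of two means and makes no allowance for this.

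The second issue is the fallback. If a region has infants on only one formula, its region-specific difference cannot be estimated, and neither can any average that includes it. That is a rank deficiency in the fixed effects, not a failure of the likelihood to converge. The fit can finish normally and return no estimate for the primary contrast, and section 6.8 has no rule for that event. A region with one or two infants on a formula also converges and simply returns a wide interval. In either case the analyst would be tempted to choose the decisive model after seeing the data.

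**Working it through.** **Inputs from the SAP (section 5).** Evaluable infants: 64 BBN-102 and 104 Brand. SD 6.0 g/day, margin 3 g/day, one-sided alpha 0.025, stated power approximately 90%. True difference taken as 0.

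**Reproducing the plan's figure.** Var = 36 × (1/104 + 1/64) = 0.909, so SE = 0.953. Power = Φ(3/0.953 − 1.96) = 88.2% (87.9% by noncentral t). This agrees with the stated figure to within rounding. The enrolment figures also reproduce: 64/0.75 ≈ 86 and 104/0.75 ≈ 139.

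**With the interaction and equal region weights.** For K regions with c_k Brand and t_k BBN-102 infants, treating Day 120 as a single time point:

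- With interaction: Var = (36/K²) × Σ(1/c_k + 1/t_k).
- Pooled site as main effect only: Var = 36 / Σ[c_k t_k/(c_k + t_k)].

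If both formulas are spread over regions with the same shares p_k, the ratio of the two variances is (1/K²) × Σ(1/p_k). The shares below are assumptions, because the documents give none.

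| Region shares | Variance ratio | SE | Power |
|---|---|---|---|
| 4 equal | 1.00 | 0.953 | 88% |
| 60/40 | 1.04 | 0.973 | 87% |
| 40/35/25 | 1.04 | 0.972 | 87% |
| 35/25/20/20 | 1.05 | 0.978 | 87% |
| 35/30/20/15 | 1.12 | 1.007 | 85% |
| 40/30/20/10 | (2.5 + 3.33 + 5 + 10)/16 = 1.30 | 1.088 | 79% |
| 50/30/15/5 | (2 + 3.33 + 6.67 + 20)/16 = 2.00 | 1.348 | 60% |

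The main-effect model has SE 0.953 and power 88% in every row.

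**Allowing for the repeated visits.** The model has no three-way formula-by-site-by-visit term, so the site-specific part of the formula effect is constant over time and draws on all five post-baseline visits. I assumed equal visit variances, complete data, and compound symmetry or AR(1) with correlation 0.5 to 0.9. Power is then 80-84% for 40/30/20/10 and 62-75% for 50/30/15/5. The single-time-point figures are therefore the pessimistic end.

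**Arms spread differently over regions.** Take Brand 40/30/24/10 and BBN-102 34/20/8/2, again at a single time point. With the interaction, SE = (6/4) × √0.904 = 1.427 and power is 55.7%. With pooled site as a main effect, SE = 0.973 and power is 87.0%.

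**Estimability.** Take Brand 40/30/24/10 and BBN-102 36/20/8/0. The formula, region and formula-by-region design has rank 7 instead of 8, and the least-squares-mean contrast lies outside its row space, so it is not estimable. Without the interaction the same data give an estimable contrast, with SE 0.987 and power 86.0%.

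**The case against.** - **The SAP never asks for equal weights.** A reader might infer that the plan prescribes them. It does not: the weights are unspecified, and equal weighting follows only from the usual default. An observed-margins option would restore most of the power (88.2% with arms spread alike, 83.8-86.0% in the unlike layouts tried). This stands, though such weighting does not repair an empty cell.
- **Pooling already addresses small sites.** It does in part, and mild imbalance after pooling costs little. But no minimum size is set, so nothing rules out the less favourable layouts.
- **An empty cell is hypothetical.** No section says that the sites changed between phases, and the 129 phase-one Brand infants may cover every region. It would be wrong to infer that the contrast will fail. What stands is that nothing in the design prevents it: randomization ignores site, nearly all Brand infants come from phase one, and all BBN-102 infants come from phase two.
- **The error is in the safe direction.** If the formula effect is similar across regions, the equally weighted contrast is unbiased, and a wider interval makes non-inferiority harder to claim. The documents do not support reading this as a route to false non-inferiority.
- **Deviations would be visible.** Section 1 requires them in the study report, and section 6 labels analyses after unblinding as post hoc. That gives transparency but does not supply a pre-specified fallback.

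**Conclusion.** The gap in specification is certain; the size of the loss is conditional. The primary decision rests on a contrast whose region weights and minimum cell size are not stated, with a fallback keyed to the wrong event. Under default equal weights and assumed region shares, the loss against 88% runs from nil (equal regions) through about 1 to 4 points (mild imbalance) to power of about 79-84% (40/30/20/10) or 60-75% (50/30/15/5). Those figures assume both formulas are spread alike and leave out any precision gained from sex, age and baseline.

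The harm is lost precision and a possible data-driven choice of model. Nor does the term reach every secondary endpoint, as one might suppose. It appears in the growth MMRMs (sections 9.2.1 to 9.2.3), the GI tolerance models (11.2) and the ICQ model (11.2.6), but formula intake (9.2.4) is compared by two-sample t-test with no site term. Should-fix.

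**What to change.** Remove the formula-by-pooled-site interaction from the primary MMRM in section 9.1 and from the models in sections 9.2.1 to 9.2.3, 11.2 and 11.2.6, and amend the covariate list in section 6.8 to match. Keep pooled site as a main effect. Fit the interaction as a supportive consistency check, reporting region-specific differences with confidence intervals. Delete the non-convergence clause in 6.8, or replace it with a fallback suited to the simpler model.

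If the sponsor prefers to keep the interaction, the SAP should fix the least-squares-mean weights, a minimum number of infants per formula per region with a rule for merging regions, and a fallback for a non-estimable contrast. Weights alone would not be enough.

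The cost is SAP text in the sections named, settled before unblinding. Nothing changes in conduct or data collection. In the layouts tried, the main-effect model gives 86-88% power and stays estimable with an empty cell.
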